### Sample size estimates

The sample size was estimated based on data from a previous feasibility study using an assumed difference of 3.8 seconds on the TUG test [9]. Thus, a sample of 45 participants will achieve a power of 0.81 in repeated measures using GEE at α = 0.05. With an anticipated 10% attrition, 50 participants will be recruited.

### Statistical analysis

Participant baseline characteristics will be compared using independent t tests (continuous variables) or Chi-Square test (categorical variables). The Shapiro-Wilk test will be used to check for normality. Feasibility measurements (safety, reach, retention, adherence) will be calculated. Changes in functional mobility and global disability, movement-related behaviours, functional and quality of life outcomes across time (baseline to immediately post intervention to follow-up) will be determined using mixed-effects models. Compositional associations between movement-related behaviours and functional outcomes will be analyzed using compositional data analysis. We will consider the moderating effect of cortical infarct volume and leukoaraiosis on outcomes.

### Safety and adverse monitoring

Safety concerns were first considered in the feasibility study, in which no adverse events were reported. Patients will be closely monitored by the study team during assessments. Furthermore, before participants complete any walking tests such as the 6-min walk test, a safety screen will be conducted to ensure there are no “red flags” or contraindications to activity. If a patient’s condition worsens significantly or if the patient requests to end their involvement in the study, all data collection will be stopped immediately, and their participation in the study will be terminated.

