**Methods:**

The study is an assessor-blinded, single-center, parallel-group, randomized controlled trial to be completed within 24 months from July 12, 2023 to June 30, 2025. We will enroll 50 patients with acute ischemic stroke within 7 days from symptom onset, aged 18 years or older, and with ongoing walking goals. Demographic and stroke characteristics, including stroke risk factors, neuroimaging, and acute stroke treatments, will be determined and documented. All participants will wear an accelerometer for one week at three different time-points (baseline, 6, and 12 weeks) to assess movement-related behaviours. Following randomization, participants in the intervention arm will receive a ‘sit less, move more, sleep better’ program for up to 1 hour/day, 5 days/week, for 6 weeks to enhance self-efficacy for change. Participants in the control arm will receive usual inpatient and early supported stroke discharge care. The feasibility outcomes will include reach (enrolled/eligible), retention (completed/enrolled), adverse events, and program adherence. Other outcomes at 6 and 12 weeks include the modified Rankin Scale, Timed-Up and Go, movement-related behaviours, walking endurance, gait speed, cognition, stroke severity and quality of life. Mixed-effects models will assess changes in outcomes over time. Compositional associations between movement-related behaviours and outcomes will consider covariates such as imaging markers.

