### Outcomes

Feasibility outcomes will be assessed including safety and adverse events, reach, retention/attrition, and adherence/intervention fidelity as outlined in Table 1. Other outcomes will include global disability assessed using the validated 6-item modified Rankin Scale (mRS) that is a valuable end point for RCTs of acute ischemic stroke trials [32]. Functional mobility will be assessed using the Timed Up and Go (TUG) test, validated in people with stroke, with a minimal detectable change of 3.53 seconds [33,34]. Time spent in movement-related behaviours (sleep, sedentary behaviour, and physical activity) will be measured with activPAL accelerometer also validated in people with stroke [27]. Additionally, self-reported sleep quality will be assessed with the widely used Pittsburgh Sleep Quality Index [35]. Gait speed will be assessed with 10-Meter Walk Test, with a change of 0.16 meters/second in comfortable gait speed considered clinically important early poststroke [36,37]. Walking endurance will be tested with the 6-Minute Walk Test, with a minimal detectable change (MDC) of 54.1 meters poststroke [38]. The reliable and widely used National Institute of Health Stroke Scale (NIHSS) [39] will be used to classify stroke severity, and the Montreal Cognitive Assessment (MOCA) to assess cognitive impairment with good predictive value in acute stroke [40]. Quality of life will be assessed using the Euro-QOL 5D (EQ-5D) validated in people with stroke [41].

**Table 1 pone.0290515.t001:** Feasibility metrics.

**Feasibility**	Safety/adverse events Reach (recruitment, refusal rates) Retention/attrition rates Adherence/intervention fidelity	Record of any adverse events (i.e. falls) Number enrolled/number eligible, including refusal % enrolled who complete the study Record flow of participants through the study

MRI imaging will be collected only at baseline. Cortical infarct volume and leukoaraiosis will be determined from MRI scans, analyzed using standardized automated segmentation protocol of fluid-attenuated inversion recovery sequences, independent of demographic or clinical data.

We will report protocol deviations and the study data will be examined for outliers, normality and missing data. Identifying potential sources of missing data is essential for mitigating these issues in a definitive trial.

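### One rule ends all data collection both for withdrawal and for significant worsening, so disability, mobility and safety data after a deterioration are lost because of it

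*Protocol article*

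**What the plan says.** The section Safety and adverse monitoring gives one rule with two triggers. If a participant's "condition worsens significantly or if the patient requests to end their involvement in the study, all data collection will be stopped immediately". The same sentence goes on to end that person's part in the trial. It does not separate stopping the intervention or a walking test from stopping outcome and safety follow-up.

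The places this rule touches:

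- **Outcomes and timing** (Abstract, Methods): "Other outcomes at 6 and 12 weeks include the modified Rankin Scale, Timed-Up and Go", followed by movement behaviours, walking tests, cognition, stroke severity and quality of life.
- **Analysis** (Statistical analysis): changes "across time (baseline to immediately post intervention to follow-up) will be determined using mixed-effects models".
- **Missing data** (Outcomes): the data will be examined for missingness, because "Identifying potential sources of missing data is essential for mitigating these issues in a definitive trial".
- **Feasibility** (Abstract, Methods): the metrics include "retention (completed/enrolled), adverse events, and program adherence". Table 1 expresses retention as the percentage "enrolled who complete the study" and safety as a log of any adverse events.

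**The concern.** Withdrawal of consent and clinical worsening are different events. After withdrawal, ending new data collection is proper. After worsening, the participant may be willing to be followed, and the later state is what the disability, severity and mobility scales exist to register. The mRS in particular can be scored in someone who can no longer walk.

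Under the rule as written, a value is missing because the participant deteriorated. A mixed-effects model uses whatever was observed earlier and is valid if missingness depends only on those observed values. When the decline happens between visits, nothing observed reflects it, so the model in effect predicts the missing values from participants who did not worsen. Examining missing data afterwards cannot recover what the protocol told staff not to collect.

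At stake is the estimated effect on mobility and global disability, which the Objective names beside feasibility. The later safety record is also affected: the course of the triggering event and anything after it, including death, falls outside collection.

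**Working it through.** **1. The plan's own figure.** Sample size estimates gives 45 evaluable participants and 10% attrition: 45 / (1 − 0.10) = 50, as stated. The allowance is 50 × 0.10 = 5 losses. The figure is right, and nothing in this point depends on it being wrong.

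**2. Retention.** Retention is completed/enrolled, so a stopped participant stays in the denominator. With k of 50 stopped, retention is 1 − k/50: 98% for k = 1, 94% for k = 3, 90% for k = 5. Worsened participants therefore lower retention and do not vanish from it. What is lost is the distinction between worsening and unwillingness, which share one count.

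**3. mRS, hypothetical.** All inputs are assumed: 25 per arm (50 at 1:1), mean mRS 2.5 in those who do not worsen and 5.5 in those who do, equal non-worsened means in both arms, and no post-baseline mRS in the worsened. Arm mean = ((25 − n) × 2.5 + n × 5.5) / 25, where n is the number worsened.

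| Worsened, intervention vs control | Intervention mean | Control mean | True difference | Observed under the rule |
|---|---|---|---|---|
| 5 vs 1 | 77.5/25 = 3.10 | 65.5/25 = 2.62 | +0.48 | 0 |
| 1 vs 3 | 65.5/25 = 2.62 | 71.5/25 = 2.86 | −0.24 | 0 |
| equal numbers | same | same | 0 | 0 |

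The true difference is (5.5 − 2.5) × (n intervention − n control) / 25, or 0.12 grades per excess worsened participant. Halving the assumed gap to 1.5 grades halves it: 5 vs 1 would give 1.5 × 4 / 25 = +0.24. The observed 0 follows from the assumption of equal non-worsened means; it is not a finding.

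**4. Does the mixed model repair it? TUG, hypothetical.** I used a simulated random-intercept model at baseline, 6 and 12 weeks (12 runs of 2,000 participants). Assumed inputs: SD 4.5 s, within-person correlation 0.7, and +15 s at both later visits after worsening. The effect in non-worsened participants was set to −3.8 s, the size of the difference in Sample size estimates. The rule was applied by deleting both later visits of worsened participants. The expected all-participant effect is −3.8 + 15 × (rate on intervention − rate on control).

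| Worsening, intervention / control | Expected | All followed | Under the rule |
|---|---|---|---|
| 5% / 5% | −3.8 s | −3.79 s | −3.85 s |
| 15% / 5% | −2.3 s | −2.25 s | −3.83 s |
| 5% / 15% | −5.3 s | −5.32 s | −3.84 s |

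Under the rule the model returns about −3.8 s whatever happens to those who worsen. With these inputs the bias is about 1.5 s in either direction when the rates differ by 10 percentage points, and near zero when they are equal.

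**5. Safety.** Table 1 logs any adverse event, so the event that triggers the stop can be recorded. Events after it cannot, if all collection has ended.

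**The case against.** A reader might infer that the worst outcomes disappear by rule from mRS, TUG, retention and safety alike, and that a harmful or protective treatment would show no mRS difference. The documents do not support that.

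- Retention keeps stopped participants in its denominator, and Table 1 plans a record of participant flow, where reasons for leaving could be shown.
- The triggering event can be entered as an adverse event, so a between-arm difference in deterioration could still appear there.
- The rule applies only to significant worsening. Lesser declines, and every value before the trigger, stay in the analysis; someone who worsens after week 6 keeps the week-6 values.
- The numerical examples are invented. On a scale ending at 6 for death, a mean of 5.5 implies that at least half of the worsened die. The protocol enrols medically stable people able to walk at least 5 metres and reports no adverse events in the earlier feasibility study.
- Feasibility outcomes are listed first, mRS and TUG come under other outcomes, and a larger trial is foreseen.

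All of this stands, and it limits the claim and its severity. It does not remove the core. The sentence cannot be read as stopping a single walking test, because participation in the study ends. It is a stated rule on collection, so no later analysis plan can undo it. The effect on mobility and disability is also a stated aim, and the sample size rests on TUG.

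**Conclusion.** The point holds in a limited form. Followed as written, the rule leaves 6- and 12-week outcomes after significant worsening, and adverse events after the triggering one, uncollected for a reason tied to the outcome. The mixed-effects models do not correct this, so the estimated effects on disability and mobility can be biased if worsening differs between arms.

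The size and direction cannot be known from the document, which gives no worsening rates. The +0.48 and −0.24 grades on the mRS and the 1.5 s on TUG rest wholly on assumed inputs and show only the mechanism. If worsening is balanced and has the same effect in both arms, the bias is near zero. Retention is not biased by removal, though it merges two reasons for leaving. Safety loses later events, not the triggering one.

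It should be corrected, but it is below must-fix for a feasibility-first trial of 50. It is worth doing soon, because the article says data collection is under way and outcomes not collected cannot be reconstructed.

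**What to change.** Split the sentence into two rules.

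1. **Withdrawal of consent:** stop new data collection and keep the data already collected.
2. **Significant worsening without withdrawal of consent:** whatever is decided clinically about the intervention and the walking tests, continue outcome and safety follow-up. Obtain the mRS at 6 and 12 weeks in person, by telephone or from the chart (death = 6), record adverse events to week 12, and keep these participants in the analysis by randomised group.

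Report the two reasons for leaving separately by arm, and leave the retention definition unchanged. TUG will still be missing in anyone who cannot or should not perform it, so the mRS is the outcome this change mainly protects.

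The cost is a protocol and consent amendment plus a few extra mRS ratings. The consent wording should ask at entry for agreement to continued follow-up after worsening, because a participant who deteriorates may be unable to reconfirm it later. The change sets no rule on treatment or on when a test should be stopped.

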## Discussion and summary

Despite rapid advances in acute stroke care, stroke remains the leading cause of adult disability globally [42]. It is concerning that survivors of stroke spend most of their time in sedentary behaviours [8], including during stroke rehabilitation [7]. Responsible factors may include poor patient compliance with assigned tasks outside of structured therapy or limited dose of rehabilitation after stroke. A meta-analysis showed that each additional hour of sedentary time, beyond 11 hours per day, increases the risk of stroke by 21% in the general population [43]. The influence of sedentary behaviour on stroke recurrence is unknown. The field of stroke recovery, rehabilitation, and restorative neuroscience is still young, and this project will contribute to our understanding of the effect of a whole-day approach to rehabilitation early poststroke.

Integrating the knowledge around mechanisms of stroke recovery, biomarkers, and development of targeted interventions to inform precision rehabilitation is a main challenge in rehabilitation science. Rehabilitation intervention studies, accounting for the heterogeneity in stroke, will ensure that the right patient receives the right intervention at the right time point after stroke with the right outcome measurement that is responsive to change [44]. Using a combination of behavioural and imaging markers may help to better understand and personalize rehabilitation early after stroke to optimize function and recovery.

The whole-day approach to promote activity, reduce sedentary behaviour, and optimize sleep may be beneficial for many people with stroke, particularly poor responders to conventional rehabilitation poststroke. Personalized intervention using theory-based behaviour change techniques could lead to a paradigm shift in how rehabilitation care is delivered early after stroke. Future research would explore a larger implementation trial of this approach to poststroke rehabilitation.
